At Chittagong Medical College Hospital (CMCH), the current practice is to start early enteral feeding through a NG-tube, with a volume of 2-4ml/kg per feed every 2 hours, avoiding 2 late night feeds, resulting in a total of 10 feeds per day for adults. For children fluid supplementation is as follows: for age 2-4years: 100 - 120ml/kg/day; 4-8yrs 90-100ml/kg/day; 8-12yrs 70-90 ≥12 yrs 60-70ml/kg/day given every 2 hours round-the-clock. In both the cases the enetral feeding volume is derived from total volume subtracting the volume given as i.v. fluids. The feeds are prepared from locally available food by blending or commercially available powder form. Although not formally assessed, aspiration pneumonia is a rather common complication of NG feeding in CMCH. Factors that can contribute include the supine position of the patient and no check for gastric retention before the next feeding. We here propose a randomized trial to compare the start of early versus late nasogastric tube feeding, with aspiration pneumonia, incidence of hypoglycaemia and coma recovery times as primary outcome measures.

Materials and Methods

*Place and Period of Study*

It is planned to study 124 consecutive patients, age 2 y/o, with cerebral *Plasmodium falciparum* malaria, defined as a Glasgow Coma Score (GCS) below 11or BCS <3 (for pre-verbal children) and the presence of asexual stage *P. falciparum* parasites in a peripheral blood slide, admitted to Chittagong Medical College Hospital, Chittagong, Bangladesh. Patients will be recruited from the internal medicine wards (ward 13, 14, and 16) and from the paediatric ward.

*Inclusion Criteria*

1. Cerebral falciparum malaria defined as a GCS<11or BCS <3 (for pre-verbal children), and the presence of asexual forms of *P. falciparum* in the peripheral blood smear.
2. The attending relative able and willing to give informed consent.
3. ≥2 years of age

*Exclusion Criteria*

1. Relatives unable or unwilling to give informed consent.
2. Patients who already have the features of aspiration pneumonia.
3. Pregnancy
4. Diabetic requiring insulin
5. Contraindications to enteral feeding:

-Circulatory shock

-Mechanical bowel obstruction / ileus / ischaemic colitis (redcurrant jelly stools)

-Severe diarrhea (> 6 per 24 hours), severe vomiting (> 6 per 24 hours) or severe dehydration due to either

-Pancreatitis (laboratory confirmed: serum amylase >500 U/L)

6. Known allergies to artesunate or quinine

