7. Severely malnourished child (according to WHO criteria)

*Examination and Treatment*

On enrolment a full history and physical examination will be carried out. Nutritional status of the patient will be assessed by skin-fold thickness in the triceps region of the left arm and the mid upper arm circumference will be measured. Weight/height and presence of bilateral pedal edema (WHO criteria) for malnourished children will be assessed.

First line antimalarial treatment will be with intravenous artesunate, if available. Artesunate (Guilin No 2 Pharmaceutical Factory, Guangxi, Peoples’ Republic of China) will be given in a dose of 2.4 mg/kg body weight on admission, then at 12 hours, 24 hours, and thereafter once daily until oral medication can be taken reliably. Each 60 mg vial contains anhydrous artesunic acid which is dissolved initially in 1 ml 5% sodium bicarbonate and then mixed with 4 ml of 5% dextrose before injecting as a bolus into an indwelling intravenous cannula. When the patient has recovered sufficiently to take tablets, a full adult course of artemether-lumefantrine (CoartemR) will be given: 4 tablets twice daily for 3 days. Currently injectable artesunate is not registered yet in Bangladesh for the treatment of severe malaria. In case artesunate for injection is not available, the patient will be treated with i.v. quinine. A loading dose of 20 mg/kg will be given over 4 hours time followed by a dose of 10 mg/kg over 2 to 4 hours every 8 hours for a total of 7 days, or until the patient has recovered sufficiently to take tablets, in which case a full course of coartem will be given (see above). Patients will be managed in accordance with the World Health Organization guidelines 2006.

*Treatment allocation*

All patients will receive a NG tube. Patients will be randomized to either receive enteral feeding upon admission through the NG tube *(arm 1)*, or no feeding until able to take oral food or maximum until 60 hours (adults i.e. >12 years old) or 36 hours (children i.e. <12 years old) after admission followed by enteral feeding *(arm 2)*. The feed used in the study will be Revit-R/Renovit(patient with renal insufficiency) (Fasska SA, Louvain la Neuve, Belgium. The preparation comes as a powder, which will be dissolve in bottled water according to the instructions of the manufacturer (220g per liter water which will provide 1 kcal/ml) The feeding protocol is as follows:

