Check position of NG tube before start of the first feed with a large syringe and before subsequent feeds by checking the position of a mark drawn on the tube at the time of insertion. Position the patient in the head tilt position (head 15° above horizontal). Start NG feeding with 2-4 ml/kg feeding every 2 hours in adult 10 feeds per day; omitting 2 late night feeds, this will deliver1000-2000kCal per 24 hours for adults weighing 50 kg. For children, the volume of enteral feeding will be calculated from the total amount of fluids to be given per 24 hours as follows: for age 2-4years: 100 - 120ml/kg/day; 4-8yrs 90-100ml/kg/day; 8-12yrs 70-90 ≥12 60-70ml/kg/day. The enteral feeding volume is derived from this total volume subtracting the volume given as i.v. The total amount of enteral feeding in children is divided in 12 feeds, given every 2 hours round-the-clock

Gastric retention will be measured just before the next feeding. Gastric retention is defined as> 4 ml/kg in adult and >2/3rd of the 2 hours previous feed in children. If gastric retention is present: feeding is discontinued and prokinetic drugs domperidon suppositories are added for adults domperidon 20 mg suppositories, every 8 hours; for children: domperidone suppository 15mg 1/2 suppository up to 5 years & 1 suppository beyond 5 years. In adults retention is reassessed 4 hourly. If the retained volume is <4 ml/kg, discard this volume, and feeds are continued every 2 hours as before. In children retention reassessed 2hourly and if the retention is < 2/3rd of the previous 2 hours feed this volume discard it, and feeds are continued every 2 hours as before.

Adult patients in the control arm (delayed start of enteral feeding) will receive 50-60ml 5% DS (glucose-saline)/kg/24 hours. The energy contents the infusion fluid containing 50-60g dextrose per liter around 200 kCal per liter, so that the energy given is 10-12 kCal/kg/ 24 hours, or 500-600 kCal for the average 50 kg patient. Paediatric patients in the control arm (arm 2) will receive 10% Dextrose in half strength saline (10% dextrose in 0.45% NaCl) in the volumes as above. This contains 400kCal/L, so that daily total calories delivered to the children not receiving enteral feeding will be for 2-4 y/o: 40-48 kCal/kg, for 4-8 y/o: 36-40 kCal/kg and for 8-12 y/o: 24-28 kCal/kg.

Family members will be instructed in the techniques for checking NG tube position using a pre-drawn mark, checking for gastric retention and giving NG feeds.

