Aspiration pneumonia will be diagnosed clinically from history and chest examination (fever, respiratory distress, auscultatory crackles, oxygen saturation), and confirmed by chest X-ray (CXR). All patients will have a CXR upon admission. If possible, a CXR will be done in the radiology department of CMCH. If the patient is not transportable, a bed side CXR will be performed. The CXR will be repeated upon indication and 3 days after the first one for follow-up. Treatment will be with antibiotics (intravenous ceftriaxone in combination with metronidazole). Oxygen will be given by nasal cannula or face mask where indicated. In the case of severe respiratory insufficiency, a concerted effort will be made to transfer the patient to the intensive care unit of CMCH for mechanical ventilation.

Analysis

*Primary outcome measures include:*

1. Incidence of aspiration pneumonia.
2. Incidence of hypoglycaemia (<2.2 mmol/L).
3. Coma recovery time. The coma recovery time is defined as the time till a Glasgow Coma Score of 15/15 (BCS 5/5 in preverbal children).

*Secondary outcome measures include:*

1. Incidence of sepsis.

Sepsis is defined as the presence of infection (other than malaria) in combination with systemic inflammatory response syndrome (SIRS) as indicated by ≥ 3 of the following criteria: prolonged fever i.e. axillary temperature  38ºC or core temperature of  36ºC; a heart rate of  90 beats/min; a respiratory rate of  20 breaths/min (up to 5yrs 40) or the use of mechanical ventilation for an acute respiratory process; a white-cell count of  12 x 109/l or  4 x 109/l, or a differential count showing > 10% immature neutrophils.

2. Time to sit independently, which will be assessed daily.

3. Time to speak independently, which will be assessed daily.

4. Time to eat independently, which will be assessed daily.

5. Total duration (days) of admission in the hospital.

6. Survival. In hospital mortality will be recorded.

Sample size calculation

To detect an increase in incidence in aspiration pneumonia from 10% to 30%, a sample size of 124 (62 in each treatment group) is required. After this pilot study the data will be analysed. If early enteral feeding appears to be promising regarding a decrease in hypoglycaemia or a shortening of coma recovery times, not at the expense of a significant increase in aspiration pneumonia, a larger follow-up trial will be planned.

Randomisation

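### Aspiration pneumonia needs X-ray confirmation, but the confirming finding is undefined, need not be new since admission, and no masked reading is described in a visibly open comparison

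*Protocol*

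**What the plan says.** The outcome is defined in the Protocol under Aspiration pneumonia. "Aspiration pneumonia will be diagnosed clinically from history and chest examination", with four items listed in brackets (fever, respiratory distress, crackles, oxygen saturation), and the same sentence goes on "and confirmed by chest X-ray (CXR". So the film is a required part of the diagnosis.

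The film schedule follows: "All patients will have a CXR upon admission", and then "The CXR will be repeated upon indication and 3 days after the first one for follow-up". Under Exclusion Criteria, entry is closed to "Patients who already have the features of aspiration pneumonia".

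The arms differ openly. Under Treatment allocation, "Patients will be randomized to either receive enteral feeding upon admission through the NG tube", while the other arm is at first not fed. All patients have a tube, but no sham feed is described. The same section adds: "Family members will be instructed in the techniques for checking NG tube position using a pre-drawn mark, checking for gastric retention and giving NG feeds".

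The outcome is used in four places:
- It is the first primary outcome (Analysis).
- It is the only basis of the sample size: 10% versus 30%, 62 per arm (Sample size calculation).
- A follow-up trial is planned only if there is no significant increase in it (Sample size calculation).
- A significant increase in the early-feeding arm stops randomisation, with interim analyses after every 50 patients (Safety).

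**The concern.** Three things are left open: what on the film counts as confirmation, whether it must be absent from the admission film, and whether the person reading the film knows the arm. A fourth is when an additional film is indicated; no trigger common to both arms is given.

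Each gap leaves room for judgement, and the expectation runs one way. The introduction says: "Although not formally assessed, aspiration pneumonia is a rather common complication of NG feeding in CMCH". The Safety section calls aspiration pneumonia an identified risk. Fever is expected in cerebral malaria without any aspiration, and no thresholds are set for respiratory distress or saturation. Because relatives give the feeds, even the history can carry knowledge of the arm.

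If suspicion is higher in fed patients, more of them may be examined closely, X-rayed and labelled, or milder cases in the unfed arm may be missed. Either would push the comparison towards harm from early feeding. The primary comparison, the stopping rule and the go decision would then err in the same direction, because all three use the same count.

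**Working it through.** **1. The plan's own figure.** Inputs from Sample size calculation: 10% and 30%, 62 per arm. Alpha and power are not stated; two-sided 5% and 80% are assumed. Pooled-variance formula without continuity correction:

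n = [1.960·√(2·0.20·0.80) + 0.842·√(0.10·0.90 + 0.30·0.70)]² / 0.20² = 61.6, rounded up to 62 per arm, 124 in total.

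This matches. There is no arithmetic error, and the assumed test is the natural one for the steps below.

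**2. How many patients separate significant from not significant.** Suppose 6 of 62 events (9.7%) in the late arm.
- 14 in the early arm: pooled rate 20/124 = 0.161; z = (8/62) / √(0.161·0.839·2/62) = 1.95, not significant.
- 15 in the early arm: pooled rate 21/124 = 0.169; z = (9/62) / √(0.169·0.831·2/62) = 2.15, significant.

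By comparison, 2, 5 and 10 percentage points of extra diagnosis in 62 patients are on average 1.2, 3.1 and 6.2 patients.

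**3. Chance of a false significant increase.** Assumptions: true rate 10% in both arms, so p_L = 0.10; extra diagnoses of d points in the early arm only, so p_E = 0.10 + d. One look at 62 per arm:

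P = Σᵢ Σⱼ Bin(i; 62, p_E) · Bin(j; 62, p_L) · 1{z(i,j) > 1.96}

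Three looks: 50 and 100 patients (about 25 and 50 per arm), then 62 per arm, each at the same unadjusted limit. The Protocol states no adjustment. The joint distribution of the two counts is carried forward from look to look, and the probability that has crossed the limit is summed.

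| Points added in early arm | One look | Three looks |
|---|---|---|
| 0 | 2.5% | 5.1% |
| 2 | 5.3% | 9.3% |
| 5 | 12.6% | 19% |
| 10 | 33.6% | 42% |

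Each column has its own unbiased reference. The rise from 2.5% to 5.1% comes from repeated unadjusted looks, a separate matter, and should not be charged to ascertainment.

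**4. The same from under-detection.** Assume a true rate of 20% in both arms, fully detected in the early arm. If 70% of late-arm cases are detected, the observed rates are 20% and 0.70·20% = 14%, and the one-look chance is 13%. If 50% are detected, the rates are 20% and 10%, and it is 34%.

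**5. What the text makes possible but does not use.** The admission film exists for everyone and a later film is scheduled, so a before-and-after comparison is available. The definition makes no reference to it. An opacity already on the admission film, in a patient without recognised features at entry, could therefore serve as confirmation later.

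**The case against.** The strongest reply is that the outcome is not a bedside impression. X-ray confirmation is mandatory. Admission and day-3 films are scheduled for all patients, so imaging is not purely discretionary. Patients with features at entry are excluded, which removes many prevalent cases. Temperature, respiratory rate and saturation are recorded every 4 hours in both arms (General care measures). All of this stands and limits the bias. It does not close the gap, because the definition neither states the confirming finding nor compares films.

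Three stronger readings are tempting and are not supported:
- *That staff who know the arm read the films.* A reader might infer this from the open design. Awareness at the bedside is a fair inference, but the Protocol does not say who reads films or what they know. The defect is its silence.
- *That the lack of a new-infiltrate rule by itself creates false harm.* Old opacities would be counted in both randomised arms alike, which tends to dilute a difference. False harm needs judgement or film ordering that depends on the arm; the loose criterion leaves room for it.
- *That the early-arm rate will be inflated by a given amount.* Nothing in the Protocol supports 10 points, or any other figure.

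It could also be said that such detail belongs in a SAP, which is not at hand. Analysis detail may. But which film finding counts, when films are taken and whether they are read masked must be settled before data are collected.

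**Conclusion.** The concern holds in limited form. For the outcome that carries the sample size, go rule and stopping rule, X-ray confirmation is required, but the confirming finding is undefined, need not be new since admission, and no masked reading is described in a visibly open comparison. Arm-dependent judgement could therefore produce or inflate an apparent increase.

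The size depends on an assumption that the Protocol cannot settle. With a true 10% in both arms, 62 per arm and unadjusted two-sided 5% tests, adding 2 to 10 points in the early arm moves the false-harm chance from 2.5% to between 5.3% and 33.6% at one look, and from 5.1% to between 9.3% and 42% over three looks. Even 5 points, about three patients, multiplies the one-look risk about fivefold (12.6/2.5). This is a design weakness worth correcting, not evidence that bias will occur. The sample size of 124 is unaffected.

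**What to change.** - Define the primary event as the listed clinical signs plus an infiltrate that is new compared with the admission film.
- Have whoever already reads the admission, day-3 and indicated films read them under a study number, without the arm.
- State the same criteria in both arms for when an indicated film is taken for outcome assessment.
- Use this reading for the primary and interim analyses. Bedside diagnosis continues to guide treatment.

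The cost is coded film requests, a few added lines in the definition, and a short delay before the reading that counts. No additional scheduled film is needed. Since the Protocol names no reader, the sponsor must confirm who reads the films, including bedside films, and that they can be kept unaware of the arm. The clinical signs will still be judged by staff who can see the feeding, so the bias is reduced, not removed.

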Although the treatment with artesunate compared to quinine considerably reduces mortality in severe and cerebral malaria, the case fatality rate remains high at between 20% and 30%[[1]](#endnote-2). Improved supportive care can importantly further reduce mortality; a series from a well equipped intensive care unit in Paris showed a mortality of 11% in patients with severe malaria[[2]](#endnote-3). Supportive treatments include highly technical aids like renal replacement therapy and mechanical ventilation, but also easier to achieve treatments like enteral feeding. In the well equipped intensive care setting early start of enteral feeding in a wide variety of patients, including those with sepsis, is now common practice. Nutrition supplies vital cell substrates, antioxidants, vitamins, and minerals, essential for normal cell function. Studies have shown that early enteral feeding preserves the barrier function of the gut, has positive effects on immune functions, is associated with a decrease in hypermetabolism and organ failure, and reduces the chance of bacteraemia [[3]](#endnote-4) [[4]](#endnote-5) [[5]](#endnote-6) [[6]](#endnote-7) [[7]](#endnote-8) [[8]](#endnote-9). In severe malaria, patients are often poorly nourished and hypoglycaemia is a common complication, especially in patients receiving quinine. Also, bacteraemia with Salmonella species is more common in severe malaria[[9]](#endnote-10), associated with increased bacterial translocation in the gut. Enteral feeding might have a beneficial effect here. The downside of starting enteral feeding in the dependent comatose patient is the risk of aspiration pneumonia; this risk is also present in the mechanically ventilated patient[[10]](#endnote-11) [[11]](#endnote-12), although the risk is lower with the use of post-pyloric enteral feeding tubes[[12]](#endnote-13) [[13]](#endnote-14) [[14]](#endnote-15). A supine position of the patient is a risk factor[[15]](#endnote-16). Routine endotracheal intubation to protect the airway in comatose malaria patients is not a feasible option in most of the tropical countries where malaria is endemic. The use of enteral feeding through a naso-gastric (NG) tube might thus induce a much higher risk of aspiration pneumonia, outweighing the theoretical benefits.

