Randomisation will be balanced in blocks of 20 by computerized method using STATA statistical software package.

Safety

Current practice in CMCH is to start on the day of admission with enteral feeding. However, if the current study shows a significant increase in the incidence of aspiration pneumonia in the group receiving early enteral feeding, randomization will be stopped, and patients will only receive enteral feeding after regaining consciousness, or 60 hours after admission. Since aspiration pneumonia is an identified risk, interim analyses will be performed after every 50 patients included. Interim data will be analysed by the Data Safety Monitoring Committee.

Benefits of the study

There is currently equipoise about the benefit of the start of early enteral feeding in patients with cerebral malaria in the tropical setting. Theoretical advantages (prevention of hypoglycaemia, restoration of immune function, etc) are countered by the increased risk of aspiration pneumonia. The study has a clear practical goal to guide this important part of the treatment of patients with cerebral malaria.

Finance

Costs involved in the study will be financed by the Wellcome Trust of Great Britain

References

1. SEAQUAMAT study group. Artesunate versus quinine for treatment of severe falciparum malaria: a randomised trial. Lancet 2005; 366: 717-725 [↑](#endnote-ref-2)

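### Coma recovery time has no value for patients who die before recovering, and the rule for going on to a larger trial does not look at mortality

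*Protocol*

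**What the plan says.** The Analysis section of the protocol lists coma recovery time as the third primary outcome: "The coma recovery time is defined as the time till a Glasgow Coma Score of 15/15 (BCS 5/5 in preverbal children". Entry requires coma: "Cerebral falciparum malaria defined as a GCS<11or BCS <3 (for pre-verbal children". The opening background says of severe and cerebral malaria under artesunate that "the case fatality rate remains high at between 20% and 30" per cent.

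Mortality comes last of six secondary outcomes: "Survival. In hospital mortality will be recorded". Total days in hospital is listed just before it.

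The Sample size section makes a follow-up trial depend on early feeding showing "a decrease in hypoglycaemia or a shortening of coma recovery times, not at the expense of a significant increase in aspiration pneumonia". The Safety section adds a stopping condition on the same harm: "if the current study shows a significant increase in the incidence of aspiration pneumonia in the group receiving early enteral feeding, randomization will be stopped". Neither rule mentions deaths.

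**The concern.** A patient who dies before GCS 15 (BCS 5) never has the event that defines the outcome. The definition gives a time only to those who recover, so the natural reading is a comparison among recoverers. That group is selected after randomisation. If one arm has more deaths, and they fall mainly on patients who would have recovered slowly, that arm's remaining recovery times are shorter although nobody recovered faster.

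This matters because shorter coma recovery alone can satisfy the efficacy half of the go rule. The rule as written can be met by an arm with more deaths, provided aspiration pneumonia is not significantly increased. Hospital stay has a more direct version of the flaw: an early death is an early end of admission and so counts as a short stay, with no link to recovery speed needed.

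**Working it through.** **1. The plan's own figure.** The Sample size section sets out the target: "To detect an increase in incidence in aspiration pneumonia from 10% to 30" per cent, with 62 per arm. Alpha and power are not given beside it; two-sided 5% and 80% are assumed.

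n = [1.96·√(2·0.20·0.80) + 0.8416·√(0.10·0.90 + 0.30·0.70)]² / 0.20² = (1.1087 + 0.4610)² / 0.04 = 61.6, so 62 per arm. The figure reproduces, and nothing below changes it.

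**2. Patients without a value.** 124 × 0.20 = 24.8 and 124 × 0.30 = 37.2: about 25 to 37 patients (12 to 19 per arm), if the cited rate applied here and deaths came before full recovery.

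**3. Size of the distortion.** Assumptions, none from the protocol: recovery times lognormal, median 48 h, log-SD 0.8, identical in both arms; 62 per arm; log-odds of death rising by a set amount per SD of log recovery time; Mann-Whitney test among survivors. Mortality is 30% with early and 20% with late feeding, the two ends of the cited range. Any 'faster' finding is false, and the nominal one-sided rate is 5%.

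| Link (log-odds per SD) | False 'faster', survivors only |
|---|---|
| 0 | 4.5% |
| 0.5 | 7.2% |
| 1.0 | 10.6% |
| 1.5 | 13.1% |

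With deaths ranked worst, the rate is about 1% or less across these links. At 25% against 20% mortality and a link of 1.5, the survivors-only rate is 8.3%. With equal mortality it is 5.3%, in effect nominal.

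A second model, with the link expressed as a correlation, gives survivor medians for 20% against 30% mortality of 48.2 and 48.1 h (correlation 0), 42.0 and 39.7 h (0.5), 39.5 and 36.0 h (0.8), and 39.1 and 35.3 h (1.0). The arm with more deaths looks up to about 4 h faster.

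**4. Censoring at death instead.** With death placed uniformly before the latent recovery time, a log-rank test at 30% against 20% and a link of 1.5 gives a false 'faster' rate of 3.5%: no inflation. Kaplan-Meier medians in the second model are 52.4 and 55.2 h (correlation 0), 48.0 and 48.9 h (0.5), 45.8 and 45.2 h (0.8), and 45.8 and 44.2 h (1.0). The direction of the apparent difference therefore depends on the unknown correlation.

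**5. How far the aspiration condition protects.** It acts only on a significant increase. At 62 per arm, power = Φ{[Δ·√62 − 1.96·√(2p̄(1−p̄))] / √(p₁q₁ + p₂q₂)}. For 10% against 20%: (0.7874 − 0.9898) / 0.5 = −0.405, so 34%. The same formula gives 13% for 10% against 15%, and 60% for 10% against 25%.

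Suppose all 10 points of excess mortality come through aspiration. The excess of aspiration pneumonia is then 10 points if every excess case dies, 10/0.75 = 13.3 points at 75% fatality and 10/0.50 = 20 points at 50%. With one final test, a control rate of 10% and aspiration drawn independently, the 13.1% falls to 8.9%, 6.2% and 2.6%. As a check, 13.1% × (1 − 0.34) = 8.6% for the first and 13.1% × (1 − 0.803) = 2.6% for the last, where 80.3% is the power for 10% against 30%.

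**The case against.** The strongest reply is that how deaths enter a time-to-event analysis is normally settled in a statistical analysis plan, which may exist but is not shown. The protocol names no test, estimator or analysis set, so a survivors-only comparison is a reading of its definition and not a stated plan. This stands as a limit. A reader might infer that the protocol commits to comparing survivors, or that its coma result must be biased; the text supports neither, and censoring at death gave no inflated log-rank result in this model. What remains is that the outcome definition and the go rule are both written in this protocol, and the go rule leaves mortality out whichever estimator is chosen.

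A reader might also take a larger error rate from a wider gap. At 35% against 20% mortality with a strong link, the survivors-only rate is about 19%. But 35% lies outside the cited range, and that figure ignores the aspiration condition.

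Nor does the go rule lack a safeguard. Where excess deaths come through aspiration, the go and stopping conditions can both act, with interim looks after every 50 patients. That blocks part of the risk, but only when the increase is significant, and not for deaths by another route.

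The 20-30% is a background figure, not a design assumption, and this trial excludes circulatory shock, so 25 to 37 deaths should not be read as the protocol's forecast. Finally, the go rule leads only to planning a larger trial after a pilot, and survival will be on record when that decision is taken.

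**Conclusion.** The point holds as a cheap improvement. The protocol gives no value to patients who die before GCS 15 (BCS 5), lets shorter coma recovery support going on, and guards that decision only against a significant rise in aspiration pneumonia.

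The distortion is conditional. It needs more deaths in one arm, deaths concentrated among slow recoverers, and a comparison among those who recover. Under those conditions, with 30% against 20% mortality, the false 'faster' rate is about 5% to 13% against a nominal 5%, before the aspiration condition takes its share. The recovery distribution and the strength of the link are assumptions, which is why a range is given. The hospital-stay flaw needs only that deaths differ between the arms.

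**What to change.** - In the Analysis section, state that coma recovery is analysed in all randomised patients and that those who die before GCS 15 (BCS 5) count as never recovered. Either give them the worst rank in a rank test, or treat death as a competing event and compare the cumulative incidence of recovery (Gray's test).
- Do not let a death count as a short hospital stay; the same convention can be used there. Carrying it over to the times to sit, speak and eat would keep the outcomes consistent.
- In the go rule, read coma recovery together with in-hospital mortality, which is already recorded. Use the estimated difference with its confidence interval and not merely the absence of significance: at 62 per arm, power for 20% against 30% mortality is only 25%.

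The cost is wording and a little more analysis. No new data are needed and the sample size stays at 124. The downside is that the result becomes a rank comparison or a recovery probability, less familiar than a plain median among survivors. That median can still be reported as a description.
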